## Overview of Trial Design

### Design

This study is a single-blinded cluster randomized controlled trial to test the effect and sustainability of the multilevel PA intervention to improve PA levels in rural older adults. There were 8 villages participating in total: 4 intervention sites and 4 control sites. RE-AIM (Research, Efficacy, Adoption, Implementation, and Maintenance) will be applied to evaluate the pre-post and intervention-control differences as well as external validity.

[figure not shown]

---

Figure 1. Overview of SAWA Intervention

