### **Randomization**

Multistage random sampling was used, and the random number was generated by the computer program ([www.random.org](http://www.random.org)). First, Chengdu was randomly selected from 18 cities in Sichuan Province. Second, Jianyang was selected out of 20 regions in Chengdu. Third, eight villages were randomly selected (Guilin, Jianzheng, Qianfeng, Yixue, Xinsheng, Yijia, Huanglian, Tiane), and these villages were further randomly assigned to either the intervention group or the control group (four villages for each group). There is a separation distance (minimum of 4 km) between each of these villages to minimize the risk of contamination.

---

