## **Data Analysis Plan**

### **1. Primary Analyses**

The primary aim will be to assess the leisure-time activity level at 8 weeks in the context of linear mixed model effects multilevel models. In this analysis, the intention-to-treat approach will be used. In addition to the intervention group, assessment time, and their interaction terms, the model may include individual-level (age, sex) variables as explanatory covariates. A random village intercept term is included to account for clustering by villages. The primary study hypothesis of SAWA will be tested based on a two-tailed significance level of 0.05.

An intention-to-treat analysis that includes all randomized participants, regardless of the number of assessments obtained, will be conducted. The analytical plans are flexible and will be adapted as scientific perspectives are advanced.

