### **2. Secondary Analyses**

#### **a. Handling of missing data**

Although substantial effort will be employed to minimize missing data, it is inevitable that some missing data will occur. Missing data are expected due to drop outs and missed visits. The leisure-time activity level is a subject-level variable and missing assessments would influence tests relative to treatment-by-time interactions. The primary analysis described above will be conducted within each dataset using linear mixed effect models and employ restricted maximum likelihood using all available data. Results of datasets will be combined to produce final estimates for between-group comparisons. This approach assumes data are missing at random: the mechanism that gives rise to missing data relies on observed data only. To assess the sensitivity and robustness of the results, we will compare results of two sets of analyses: i) all participants, with or without missing data, were subjected to the repeated measures linear mixed model analysis; ii) we will perform the linear mixed model with missing

---

data imputed using multiple imputation.

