#### b. Secondary Outcomes

All the data will be collected at the baseline, 4 weeks, 8 weeks, 6 months, 12 months, and 24 months. The secondary outcomes include household activity, work-related activity, total PA, proportions of meeting WHO recommendations, leisure-time preferences, sedentary behavior, self-efficacy, self-regulation, self-rated health, cognitive function, night-time sleep quality, weight, percentage weight change, body mass index, percentage body fat, visceral fat, waist circumference, hip circumference, waist-to-hip ratio, waist-to-height ratio, and systolic and diastolic blood pressure at all assessment time, as well as the leisure-time activity at 4 weeks, 6 months, 12 months, and 24 months. Generalized linear mixed models were used to test the effect of the intervention on the binary outcomes. For continuous outcomes, analyses will be performed using a similar strategy as the primary analyses.

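### With only 8 randomised villages, the primary mixed model names no small-sample reference distribution and no village-by-time term, so its 5% level is not secured

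*Supplement*

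**What the plan says.** All references are to the final protocol in the Supplement.

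- Design: "There were 8 villages participating in total: 4 intervention sites and 4 control sites". Under Randomization the village is the unit of allocation, with "four villages for each group".
- Outcomes: the primary outcome is the change in leisure-time activity at 8 weeks. The opening of Primary Analyses speaks instead of the level at 8 weeks.
- Primary Analyses, fixed effects: "In addition to the intervention group, assessment time, and their interaction terms, the model may include individual-level (age, sex) variables as explanatory covariates". Random effects: "A random village intercept term is included to account for clustering by villages". Level: "The primary study hypothesis of SAWA will be tested based on a two-tailed significance level of 0.05".
- Handling of missing data: the models "employ restricted maximum likelihood using all available data".
- Secondary Outcomes: "Generalized linear mixed models were used to test the effect of the intervention on the binary outcomes". Continuous secondary outcomes follow the primary strategy.
- Sample Size Computation: effect size 0.42, 80% power, design effect 2.1 from a pilot, 189 per arm after clustering and 227 per arm after a 20% allowance.

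Nowhere is there a denominator-df method, a t reference, a village-level or permutation analysis, or the name of the software. Equally, nothing says that a normal reference will be used.

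**The concern.** The intervention is allocated to villages, so the information on between-village variation comes from 8 − 2 = 6 degrees of freedom, however many participants are enrolled. A random village intercept puts a village variance into the standard error. It does not by itself make the test allow for how poorly that variance is estimated.

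There is a second gap. The intercept describes villages that are persistently high or low. It does not describe villages whose activity moves differently between baseline and 8 weeks, and that is the variation that matters for a comparison of change.

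At stake are the validity of the primary p-value, the coverage of the intervals for primary and secondary outcomes, and the 80% power, which was computed without regard to 6 df.

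**Working it through.** **1. The plan's own sample size.** Normal formula: 2(1.960 + 0.842)²/0.42² = 89 per arm; the t-based version gives 90. Then 90 × 2.1 = 189; 189 × 1.2 = 226.8, rounded to 227; two arms, 454. The figures reproduce.

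**2. Implied ICC.** From DE = 1 + (n − 1)ICC:
- 189/4 = 47.25 per village: ICC = 1.1/46.25 = 0.024.
- 227/4 = 56.75 per village: ICC = 1.1/55.75 = 0.020. If ICC stays at 0.024, DE rises to 2.33.

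**3. Between-village contrast, normal reference.** With t on 6 df the critical value is 2.447, against 1.960; 2.447/1.960 = 1.25. Using 1.96 gives 2·P(t₆ > 1.96) = 0.098 and coverage 90.2%. This is the limit when the village variance is clearly above zero. REML can estimate it as zero, which lowers the error. Simulated size of the REML z test with 8 equal villages:

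| Per village | ICC | Size | Coverage |
|---|---|---|---|
| 47 | 0 (assumed) | 3.9% | 96.1% |
| 47 | 0.024 | 8.1% | 91.9% |
| 57 | 0.020 | 8.1% | 91.9% |
| 57 | 0.024 | 8.5% | 91.5% |
| 47 | 0.05 (assumed) | 9.3% | 90.7% |
| 47 | 0.20 (assumed) | 9.8% | 90.2% |

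**4. Change at 8 weeks, tested as group by time.** Write each observation as fixed effects plus village u, village-by-time w, participant p and residual e. In the change, u and p cancel. A village's mean change, with m participants, has variance 2σ²w + 2σ²e/m. The intercept-only model pools w, p and e into its residual and uses roughly 2(σ²w + σ²p + σ²e)/m. Participant correlation makes that standard error too large; village-by-time variance makes it too small.

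The documents give no variance split, so the splits below are assumptions (total variance 1, m = 47, two occasions, normal reference):

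| σ²u | σ²w | σ²p | σ²e | Village intercept only | Participant intercept added | Village-level t, 6 df |
|---|---|---|---|---|---|---|
| 0.024 | 0 | 0.5 | 0.476 | 0.5% | 5.2% | 5.0% |
| 0.019 | 0.005 | 0.5 | 0.476 | 2.4% | 10.9% | 5.2% |
| 0.012 | 0.012 | 0.5 | 0.476 | 5.9% | 18.0% | 5.0% |
| 0 | 0.024 | 0.5 | 0.476 | 12.8% | 27.7% | 5.2% |
| 0.012 | 0.012 | 0.3 | 0.676 | 8.1% | 14.4% | 5.2% |
| 0 | 0.024 | 0.3 | 0.676 | 14.7% | 22.5% | 4.9% |
| 0.012 | 0.012 | 0 | 0.976 | 12.4% | 12.3% | 5.4% |
| 0 | 0.024 | 0 | 0.976 | 17.6% | 17.4% | 4.8% |

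Hand check of row 1: true variance 2 × 0.476/47 = 0.0203; model variance 2 × 0.976/47 = 0.0415; standard-error ratio 1.43; effective cut-off 1.96 × 1.43 = 2.81, a two-sided error of 0.5%.

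**5. Power on 6 df.** Standard error = √(2·DE/N), effect 0.42.

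| N per arm | DE | Effect/SE | Power, z | Power, t₆ |
|---|---|---|---|---|
| 189 | 2.1 | 2.82 | 80% | 65% |
| 227 | 2.1 | 3.09 | 87% | 73% |
| 227 | 2.33 | 2.93 | 83% | 69% |

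**6. Permutation test.** There are C(8,4) = 70 allocations. The two smallest two-sided p-values are 2/70 = 0.029 and 4/70 = 0.057, so only the most extreme split falls below 0.05. At DE 2.1, simulated power is 49% at 189 per arm and 56% at 227.

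**The case against.** A reader might infer that the primary test runs at about 10%, declares success about twice as often as claimed under no effect, and that every 95% interval under-covers. The documents do not support this, for three reasons.

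- The plan is silent on the reference distribution. Software that uses village-level df for a between-village contrast would not show the inflation in step 3.
- Even with a normal reference, 9.8% is the limit for a between-village contrast. At the protocol's own design effect it is 8 to 8.5%.
- The primary outcome is change. For that contrast under the stated model the statistic does not follow t on 6 df, and the test may be conservative. For the same reason the df problem and the missing random effect cannot be treated as errors that simply add up.

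It can also be said that a df method is often left to a separate analysis plan, that the listed random effect need not be exhaustive (the missing-data section mentions a repeated-measures model), and that the plans are declared flexible. The first carries limited weight, because this section is itself headed Data Analysis Plan. On the second, adding a participant intercept alone makes matters worse wherever villages differ in their change and participants' repeated measures are correlated. On the third, flexibility permits a correction but does not supply one, and it leaves the reference distribution open to choice after the data are seen.

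A df option alone is also not enough. Under the intercept-only model, automatic methods treat group by time as a within-village contrast and return participant-level df.

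**Conclusion.** The concern holds in a conditional form: as written, the plan does not secure its two-sided 5% level with 4 against 4 villages. With a normal or participant-level reference, a between-village contrast has an error of about 8 to 8.5% at the ICC implied by the design effect and at most 9.8%, with coverage of roughly 90 to 92%. For change at 8 weeks under the village-intercept model, the error ran from 0.5% to 17.6% over the assumed splits, and from 5.2% to 27.7% with a participant intercept added. A village-level t test on 6 df stayed near 5% throughout.

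These figures rest on equal village sizes, normal data, the pilot design effect and assumed variance splits. They show how far the level can move; they do not predict the trial's actual error rate.

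**What to change.** Amend Primary Analyses before the analysis is run, with one of these as the primary test:

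1. A village-level analysis of change from baseline to 8 weeks, referred to t on 6 df.
2. A mixed model with participant and village-by-time random effects and Kenward-Roger or Satterthwaite df, falling back on 6 df if the village variance is estimated as zero. The fallback is needed because, for a between-village contrast at DE 2.1, that happens in about 17% of trials (P(χ²₆ < 6/2.1) = 0.173), and model-based df can then revert towards participant level. Using 6 df with the REML standard error is somewhat conservative: simulated size 3.5 to 3.8% at the implied ICC.

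State whether the tested quantity is the change or the level at 8 weeks. For binary outcomes, use a village-level analysis or a t reference on 6 df. A permutation test over the 70 allocations can be supportive only.

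This needs no new data, but it changes the model as well as a software option. Intervals will be about 25% wider than with z. Sample Size Computation should restate power as about 65% at 189 per arm, or about 69 to 73% if all 227 per arm are analysed, in place of 80%.

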### **2. Secondary Analyses**

#### **a. Handling of missing data**

Although substantial effort will be employed to minimize missing data, it is inevitable that some missing data will occur. Missing data are expected due to drop outs and missed visits. The leisure-time activity level is a subject-level variable and missing assessments would influence tests relative to treatment-by-time interactions. The primary analysis described above will be conducted within each dataset using linear mixed effect models and employ restricted maximum likelihood using all available data. Results of datasets will be combined to produce final estimates for between-group comparisons. This approach assumes data are missing at random: the mechanism that gives rise to missing data relies on observed data only. To assess the sensitivity and robustness of the results, we will compare results of two sets of analyses: i) all participants, with or without missing data, were subjected to the repeated measures linear mixed model analysis; ii) we will perform the linear mixed model with missing

---

data imputed using multiple imputation.

#### b. Secondary Outcomes

All the data will be collected at the baseline, 4 weeks, 8 weeks, 6 months, 12 months, and 24 months. The secondary outcomes include household activity, work-related activity, total PA, proportions of meeting WHO recommendations, leisure-time preferences, sedentary behavior, self-efficacy, self-regulation, self-rated health, cognitive function, night-time sleep quality, weight, percentage weight change, body mass index, percentage body fat, visceral fat, waist circumference, hip circumference, waist-to-hip ratio, waist-to-height ratio, and systolic and diastolic blood pressure at all assessment time, as well as the leisure-time activity at 4 weeks, 6 months, 12 months, and 24 months. Generalized linear mixed models were used to test the effect of the intervention on the binary outcomes. For continuous outcomes, analyses will be performed using a similar strategy as the primary analyses.

### **3. Subgroup Analyses**

Modification of the effect of intervention upon primary and secondary outcomes will be performed separately in subgroups including age groups, sex, education level, household income, and BMI at baseline. Tests for key interactions (different intervention effects between sub-groups) will also be performed. However, it is recognized that the study may not be powered adequately to detect interactions; all subgroup analyses will be considered exploratory.

---

## **Trial Organization**

The Principal Investigator will oversee and monitor progress to reach the milestones with decisions concerning short-term goals and the evaluation of longer-term progress being discussed with the research staff via weekly meetings. The research team will be organized into sub-teams of investigators and staff. The overall organizational structure will be reviewed and amended as required.

### **Intervention Team**

The Intervention Director will lead the intervention team, which will consist of health psychology, health literacy, and physical activity experts who will develop the intervention materials.

### **Assessment Team**

The Assessment Director will lead the assessment team, which will consist of data collection technicians trained by the assessment director and experts in anthropometry, questionnaire administration and health literacy. The assessment team will be responsible for collecting data on the outcome measures at baseline, 4-week, 8-week, 6-month, 12-month, and 24-month visits.

### **Education Team**

The Director of Education and his/her team will be responsible for developing an educational program on PA for the intervention group in the trial.

## Timeline

The SAWA trial is designed as an 8-week intervention for rural older adults. The overall duration of this study is four years. The following figure shows the timeline of activities (by quarter) for the SAWA trial.

| Activities                                  | 2020 |   |   |   | 2021 |   |   |   | 2022 |   |   |   | 2023 |   |   |   |
|---------------------------------------------|------|---|---|---|------|---|---|---|------|---|---|---|------|---|---|---|
|                                             | 1    | 2 | 3 | 4 | 1    | 2 | 3 | 4 | 1    | 2 | 3 | 4 | 1    | 2 | 3 | 4 |
| Trial Registration                   |      |   |   |   |      |   |   |   |      |   |   |   |      |   |   |   |
| Pre-intervention Preparation         |      |   |   |   |      |   |   |   |      |   |   |   |      |   |   |   |
| Training of Outcomes Assessment Team |      |   |   |   |      |   |   |   |      |   |   |   |      |   |   |   |
| Participants Recruitment             |      |   |   |   |      |   |   |   |      |   |   |   |      |   |   |   |
| Intervention                         |      |   |   |   |      |   |   |   |      |   |   |   |      |   |   |   |
| Follow-up Visits                     |      |   |   |   |      |   |   |   |      |   |   |   |      |   |   |   |
| Data Analysis                        |      |   |   |   |      |   |   |   |      |   |   |   |      |   |   |   |
| Publications                         |      |   |   |   |      |   |   |   |      |   |   |   |      |   |   |   |

Figure 3. Timeline of Activities (by Quarter) for the SAWA Trial.

---

## **Appendices**

**Appendix A:** SAWA Forms and Questionnaires

**Appendix B:** Intervention Materials

**Appendix C:** SAWA Recruitment Materials

---

## **Appendix A: SAWA Forms and Questionnaires**

- **Baseline Demographics, Health Behavior, and Health History Questionnaire**
- **Physical Activity Scale for the Elderly**
- **Leisure-time Activity Preferences Measurement Form**
- **Sedentary Behavior Measurement Form**
- **Self-Efficacy for Exercise Scale**
- **Physical Activity Self-Regulation Scale Telephone Interview for Cognitive Status**
- **Pittsburgh Sleep Quality Index**
- **Adverse Event Log**
- **Visit Checklist**

---

## **Baseline Demographics, Health Behaviors, and Health History Questionnaire**

### **1. Basic Information**

1.1 Participant's name: \_\_\_\_\_

1.2 Village: (1) Guilin; (2) Jianzheng; (3) Qianfeng; (4) Yixue; (5) Xinsheng; (6) Yijia;  
(7) Huanglian; (8) Tiane

1.3 ID number: \_\_\_\_\_

1.4 Investigator 's Signature: \_\_\_\_\_

1.5 Date: \_\_\_\_\_

### **2. Socio-demographic Characteristics**

2.1 Sex: (1) male; (2) female

2.2 Marital status: (1) married/cohabited; (2) widowed; (3) separated/divorced; (4)  
never married

#### **4. Daily Behavior**

4.1 Smoking status. Please select the option that fits your situation.

(1) never

(2) former (quit smoking for more than six months or more)

(3) current (total smoking to date is over 100 cigarettes)

4.2 Alcohol consumption. How did you drink in the past year, including beer, wine or liquor?

(1) never / seldom; (2) < once a month; (3)  $\geq$  once a month

4.3 Daytime napping

4.3.1 I have the habit of taking daytime napping. (1) yes; (2) no (end)

4.3.2 Usually, I take daytime napping \_\_\_\_\_ day(s) a week.

4.3.3 Usually, I take an average daytime napping of \_\_\_\_\_ minutes a day.

---

## Physical Activity Scale for the Elderly

### 1. Leisure-time Physical Activity

1.1 Have you walked outside home in the past week? For example, walking the dog, exercising, and walking to and from work.

(1) never (skip to question 1.1.c); (2) seldom (1-2 days); (3) sometimes (3-4 days); (4) often (5-7 days)

1.1.a How much time do you usually spend doing these things each day?

(1) < 1 hour; (2) 1-2 hours; (3) 2-4 hours; (4) > 4 hours

1.1.b How many kilometers do you usually walk per day?

(1) < 0.5 km; (2) 0.5-1 km; (3) 1-2 km; (4) > 2 km

1.2 In the past week, how did you participate in light sports such as fishing?

(1) never (skip to question 1.2.c); (2) seldom (1-2 days); (3) sometimes (3-4 days); (4) often (5-7 days)

1.2.a What are the specific activities: \_\_\_\_\_

1.2.b How much time do you usually spend doing these things each day?

(1) < 1 hour; (2) 1-2 hours; (3) 2-4 hours; (4) > 4 hours

1.3 In the past week, how did you participate in moderate sports such as table tennis, dancing, or tai chi?

(1) never (skip to question 1.3.c); (2) seldom (1-2 days); (3) sometimes (3-4 days); (4) often (5-7 days)

1.3.a What are the specific activities: \_\_\_\_\_

1.3.b How much time do you usually spend doing these things each day?

(1) < 1 hour; (2) 1-2 hours; (3) 2-4 hours; (4) > 4 hours

---

1.4 In the past week, how did you participate in strenuous sports such as jogging, cycling, or swimming?

(1) never (skip to question 1.4.c); (2) seldom (1-2 days); (3) sometimes (3-4 days); (4) often (5-7 days)

1.4.a What are the specific activities: \_\_\_\_\_

1.4.b How much time do you usually spend doing these things each day?

(1) < 1 hour; (2) 1-2 hours; (3) 2-4 hours; (4) > 4 hours

1.5 In the past week, how did you participate in muscle strength / endurance exercises such as weight lifting, bench press, or push-ups?

(1) never (skip to question 1.5.c); (2) seldom (1-2 days); (3) sometimes (3-4 days); (4) often (5-7 days)

1.5.a What are the specific activities: \_\_\_\_\_

1.5.b How much time do you usually spend doing these things each day?

(1) < 1 hour; (2) 1-2 hours; (3) 2-4 hours; (4) > 4 hours

## **2. Household Physical Activity**

2.1 In the past week, did you participate in light housework such as washing dishes or sweeping the floor?

(1) no (skip to question 2.2); (2) yes

2.1.a How much time do you spend on light housework for a week: \_\_\_\_\_ hours

---

2.2 In the past week, did you participate in heavy housework or chores such as wiping floors, cleaning windows, or moving things?

(1) no (skip to question 2.3); (2) yes

2.2.a How much time do you spend on heavy housework or chores for a week: \_\_\_\_\_ hours

2.3 In the past week, did you participate in the following activities?

---

| Items                                                                       | Yes | No |
|-----------------------------------------------------------------------------|-----|----|
| a. Home repairs such as repairing electrical appliances, or doing carpentry | 1   | 2  |
| b. Lawn work or yard care                                                   | 1   | 2  |
| c. Outdoor gardening                                                        | 1   | 2  |
| d. Caring for another person                                                | 1   | 2  |

---

